#### Statistical analysis

Statisticians who are independent from the research team will be responsible for the statistical analysis. The SPSS 12.0 software for Windows (Chicago, IL, USA) will be used. Categorical variables will be presented with frequencies or percentages and continuous variables will be presented as mean and standard deviation. The main analysis will compare the efficacy of acupuncture treatment group with the control group, including primary and secondary outcomes. Changes in all outcome measurements before and after the treatment and between groups will be analyzed. Demographic and clinical characteristics of two groups will be compared on admission using unpaired two-sample t-tests (continuous data) and Chi-square analysis (categorical data). Nonparametric methods will be used when assumptions of normality are violated. We will also conduct an intention-to-treat analysis if participants are lost to follow-up. The statistical significance threshold will be set at 0.05 (two-sided), with 95 % confidence intervals.

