### Inclusion criteria

Participants meeting the following inclusion criteria will be included: (1) ischemic stroke that have been confirmed by computed tomography (CT) or magnetic resonance imaging (MRI); (2) 40 to 75 years old; (3) first episode of stroke or with a history of stroke but with no serious deformity and modified Ranking Scale (mRS) grade ≤ 2; (4) 2 to 20 weeks after the onset of the current stroke; (5) with unilateral lower limb cavovarus foot and can walk at least 6 meters [15]; (6) blood pressure lower than 160/100 mmHg; (7) sufficient cognition to follow commands and Mini-Mental State Examination (MMSE) score > 24; and (8) voluntary participation and informed consent signed.

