#### Basic characteristic variables

Demographic information including gender, age, ethnicity, time from the attack of stroke, use of medication and other detailed information will be collected at baseline to describe compare conditions and characteristics of two groups. Vital signs such as the resting blood pressure, pulse, respiration rate, and body temperature will be measured every day by nurses.

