#### Sample size

The current study is designed as a pilot study to investigate the biomechanical effects of acupuncture for poststroke cavovarus foot. A total of 60 patients, 30 in each group, will be recruited during the entire study. The results will provide evidence for the feasibility and sample size calculation of large-scale randomized controlled trials.

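### Outcomes are framed as before-after and between-group changes with no stated use of baseline values; a baseline-adjusted between-group contrast would be more precise, and before-after changes are not evidence of efficacy

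*Protocol article*

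**What the plan says.** All statements are in the protocol article.

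- **Main comparison** (Statistical analysis): "The main analysis will compare the efficacy of acupuncture treatment group with the control group, including primary and secondary outcomes".
- **Form of the outcome analysis** (the next sentence): "Changes in all outcome measurements before and after the treatment and between groups will be analyzed". No efficacy model, test or covariate is named.
- **Use of baseline data** (same section): "Demographic and clinical characteristics of two groups will be compared on admission using unpaired two-sample t-tests", with chi-square tests for categorical data. This is the only use of baseline characteristics that the section describes.
- **Significance** (same section): "The statistical significance threshold will be set at 0.05 (two-sided), with 95 % confidence intervals". The threshold is not limited to the between-group contrast.
- **Population** (Inclusion criteria): patients enter "2 to 20 weeks after the onset of the current stroke". Basic characteristic variables lists "time from the attack of stroke" among the data collected at baseline.
- **Treatment** (Interventions): both arms receive the conventional rehabilitation programme, and the acupuncture arm receives acupuncture in addition.
- **Size** (Sample size): "A total of 60 patients, 30 in each group, will be recruited during the entire study". The trial is called a pilot, and no power, effect size, standard deviation or correlation is given.

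**The concern.** Two things in the outcome sentence deserve attention.

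First, it takes change from baseline as the quantity to be analysed. A plain change score subtracts the whole baseline value, whereas regression on baseline subtracts only the part that predicts the outcome. Unless the two visits are very highly correlated, the plain change score carries avoidable noise. In a trial of 60 patients that noise also enters the estimates that, according to the Sample size section, will be used to plan a larger trial.

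Second, before-after and between-group changes stand side by side under one significance threshold, and nothing says what each is for. Patients in the first months after a stroke, with an hour of rehabilitation five times a week for 4 weeks, can be expected to improve in both arms. A significant before-after change in the acupuncture arm would therefore not show that acupuncture works. Comparing the two arms' before-after p-values would not show it either.

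**Working it through.** **Inputs from the protocol article.** 30 patients per arm; two-sided 0.05; assessments at baseline, 4 weeks and the end of the 3-month follow-up; entry 2 to 20 weeks after stroke. There is no power or precision figure to reproduce.

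**Assumed inputs.** The correlation r between baseline and post-treatment value (range 0.3 to 0.9); equal standard deviation (SD) at both visits; for power, a true difference of 0.5 SD; for the within-arm check, the size of a common improvement.

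**1. Precision of the between-group contrast.** In units of SD², per patient:

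- change score: 2(1 − r)
- ANCOVA on baseline: 1 − r²
- ratio: (1 − r²) / [2(1 − r)] = (1 + r)/2

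The difference, 2(1 − r) − (1 − r²) = (1 − r)², is never negative. Apart from the small cost of estimating the slope, ANCOVA therefore cannot be the less precise of the two. Power below uses the noncentral t distribution with 58 degrees of freedom for the change score and 57 for ANCOVA.

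| r | Var(change) | Var(ANCOVA) | Ratio | Patients with change scores that match 60 with ANCOVA | Power at 0.5 SD, change | Power at 0.5 SD, ANCOVA |
|---|---|---|---|---|---|---|
| 0.3 | 1.40 | 0.91 | 0.65 | 60/0.65 = 92 | 36% | 51% |
| 0.5 | 1.00 | 0.75 | 0.75 | 60/0.75 = 80 | 48% | 59% |
| 0.7 | 0.60 | 0.51 | 0.85 | 60/0.85 = 71 | 69% | 76% |
| 0.9 | 0.20 | 0.19 | 0.95 | 60/0.95 = 63 | 99% | 99% |

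The post-treatment value alone has variance 1 and gives 48% power. Below r = 0.5 the change score does worse than ignoring baseline altogether.

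**2. Adding weeks since stroke.** If it explains a further share R² of the residual variance, the standard error is multiplied by √(1 − R²): 0.975 at 5%, 0.949 at 10% and 0.894 at 20% (shares assumed). If entry were uniform over 2 to 20 weeks, the SD would be 18/√12 = 5.20 weeks. The arm means would then differ by chance within ±1.96 × 5.20 × √(2/30) = ±2.6 weeks in 95% of trials. The between-group standard error already allows for this; adjustment would recover part of it.

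**3. What before-after tests can show.** Suppose acupuncture has no effect and both arms improve by the same amount, expressed in SDs of the change. Let p be the power of a paired t-test with n = 30. The chance that exactly one arm is significant is 2p(1 − p).

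| Common improvement | p | Exactly one arm significant |
|---|---|---|
| 0.2 | 0.185 | 30% |
| 0.3 | 0.355 | 46% |
| 0.5 | 0.754 | 37% |
| 0.7 | 0.959 | 8% |
| 0.8 | 0.989 | 2% |

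The between-group test errs in 5% of such trials. The discordance is high for moderate improvement and fades when improvement is large. In that case both arms are significant, which is equally uninformative about acupuncture.

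**The case against.** A reader might infer that the efficacy analysis rests on before-after changes. The article does not support that. The sentence just before the outcome sentence makes the group comparison the main analysis, the outcome sentence itself includes the comparison between groups, and no sentence says that efficacy will be concluded from within-arm tests. The discordance figures in step 3 therefore describe a decision rule that the article neither adopts nor rules out.

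A reader might also infer bias from natural recovery or from unequal time since stroke. Randomisation balances both in expectation, so what is lost is precision. Nor would within-arm change reflect natural recovery alone, because both arms also receive rehabilitation.

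It can further be said that the article names no efficacy model, that changes can be analysed with baseline as a covariate, and that a covariate model may stand in an analysis plan that is not shown. That is fair, and silence on covariates would not be a finding by itself. What remains is what the article does state: change as the quantity analysed for every outcome, before-after analysis beside the randomised contrast without a distinction of purpose, and baseline data mentioned only for significance tests on admission.

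Finally, this is a pilot with no power claim, so the power figures correct no stated number, and at r = 0.9 the gain nearly vanishes. Both points stand and limit the weight of the concern.

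**Conclusion.** The concern holds as a point of precision and clarity of inference. The randomised contrast is the main analysis and is not biased by the wording. If it is carried out on unadjusted change scores, its variance is larger than it need be. The saving from ANCOVA is 35% at r = 0.3, 25% at 0.5, 15% at 0.7 and 5% at 0.9, assuming equal SDs at the two visits and a correlation that the article does not give.

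Before-after changes in this population combine natural recovery, rehabilitation and any acupuncture effect. They cannot serve as evidence of efficacy, and the article should say so. Because the improvement is nearly free and uses data already collected, it should be made. Nothing in the article shows that the trial's conclusions would be wrong without it.

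**What to change.** Reword the Statistical analysis section, or state in the analysis plan, that:

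1. The between-group difference in each outcome is estimated by ANCOVA of the post-treatment value on group and the baseline value of the same outcome, preferably also weeks since stroke, and is reported with its 95% confidence interval. If results are preferred as changes, using change as the response with the same covariates gives the same group difference.
2. Efficacy conclusions are drawn only from this contrast.
3. Within-arm changes are reported descriptively, without p-values.

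A minor reporting point is to make the baseline table descriptive. Under randomisation, tests on admission examine a null hypothesis that is true by design, and they correct no imbalance.

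The cost is one degree of freedom for the baseline value, or two with weeks since stroke, out of 58. No new data are needed, because the outcomes are assessed and time since stroke is recorded at baseline. Reporting the observed baseline-outcome correlation would also give the later trial the figure missing here for its sample size.

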### Informed consent

Prior to the study, the general study process and the responsibilities of the participants and researchers will be explained to potential participants. Participants will be informed that their entry into the trial is entirely voluntary and that they could withdraw at any time. In the event of their withdrawal, data collected on the participant will not be erased and will be used in the final analyses. Written informed consent should be obtained from each participant before he or she undergoes any interventions related to the study.

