### Randomization and allocation concealment

All participants will be assigned in a 1:1 ratio according to a computer-generated randomization list. Assignments will be sealed in opaque envelopes and will be opened by the study staff following informed consent procedures and baseline testing. The participants and researchers will know the allocation but the outcome assessors and data analysts will not.

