#### Adverse Events

Any adverse events during the intervention period will be reported, and the causality with acupuncture therapy will be analyzed. All adverse events will be reported to the primary investigator and ethics committee to decide if the participant needs to withdraw from the trial. In case of stroke recurrence or other worsening conditions, the patients will be discontinued from the study and will be sent for further treatment.

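### Intention-to-treat is only a conditional extra analysis, and patients who worsen leave the study itself, so the main comparison may lose follow-up values from patients with a poorer prognosis

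*Protocol article*

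**What the plan says.** Three sections of the protocol article bear on who is in the main comparison.

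- **Statistical analysis.** The main analysis comes first: "The main analysis will compare the efficacy of acupuncture treatment group with the control group, including primary and secondary outcomes". The quantity compared is change: "Changes in all outcome measurements before and after the treatment and between groups will be analyzed". No analysis set is named. Intention-to-treat comes later, as an addition with a condition: "We will also conduct an intention-to-treat analysis if participants are lost to follow-up".
- **Adverse Events.** Patients who deteriorate leave the study, not only the treatment: "In case of stroke recurrence or other worsening conditions, the patients will be discontinued from the study and will be sent for further treatment". For adverse events in general, withdrawal is decided case by case: "All adverse events will be reported to the primary investigator and ethics committee to decide if the participant needs to withdraw from the trial".
- **Informed consent.** When a participant withdraws, "data collected on the participant will not be erased and will be used in the final analyses".

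The Outcome measures section has three assessments: baseline, 4 weeks, and the end of the 3-month follow-up. No section says that a discontinued patient is assessed after leaving.

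**The concern.** If the main comparison already covered every randomised patient as assigned, a further intention-to-treat analysis that depends on losses would add nothing. The wording therefore suggests that the main comparison uses patients with follow-up data. The condition is also awkwardly placed. Loss to follow-up is the situation in which an as-randomised analysis is hardest to carry out, because the values are missing by then.

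The discontinuation rule makes this matter. Stroke recurrence and clinical worsening probably go with poorer walking and standing, so the missing values are unlikely to be a random subset. If one arm loses more such patients, the remaining groups are no longer the ones that randomisation made comparable. An intention-to-treat analysis added afterwards would have no observed endpoint for these patients and would depend on imputation.

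The trial is a pilot, but it compares efficacy at a two-sided 0.05 level, and the Sample size section says its results will support feasibility and the sample size of larger trials. A distorted effect or SD would carry into that planning.

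**Working it through.** **No figure in the plan to reproduce.** The Sample size section gives 30 + 30 = 60 without effect size, SD, power or expected loss. The point concerns the analysis set and does not depend on the sample size.

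**Step 1: what a discontinued patient contributes under the text as written.**

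| Discontinued | Values held | Change at 4 weeks | Change at 3 months |
|---|---|---|---|
| Before week 4 | Baseline only | None | None |
| After week 4 | Baseline, 4 weeks | Available | None |

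Retaining data already collected, as the Informed consent section does, keeps the values in the second column. It cannot supply the missing ones. That sentence also concerns a participant's own withdrawal, so it is unclear whether it covers patients discontinued by the study.

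**Step 2: size of the bias.** Let a fraction q of an arm be discontinued, with mean outcome k SD worse than those who remain. The mean of those who remain then exceeds the mean of the whole arm by q × k. With the same k in both arms:

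bias = (difference in q between arms) × k

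Inputs:
- 30 per arm, from the Sample size section.
- Difference in q from 0 to 0.10 (0 to 3 of 30 patients): assumed.
- k from 1 to 2: assumed.

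Results:
- Difference 0: bias = 0.
- Difference 0.10, k = 1: bias = 0.10 SD.
- Difference 0.10, k = 2: bias = 0.20 SD.

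**Step 3: compare with the precision of the trial.** With outcome SD 1 and 30 per arm:

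SE = √(2/30) = 0.258 SD

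So 0.10/0.258 = 0.39 and 0.20/0.258 = 0.77: the non-zero cases are 39% to 77% of one standard error.

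**Step 4: a severe illustration.** Suppose the lowest-scoring patients on the outcome itself are removed and the rest compared by a two-sample t-test at two-sided 0.05 (30 per arm, SD 1, no true effect, 40,000 simulated trials).

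| Removed, acupuncture / control | Bias (SD) | Type I error |
|---|---|---|
| 0 / 0 | about 0 | 0.048 |
| 2 / 1 | 0.06 | 0.076 |
| 3 / 1 | 0.12 | 0.099 |
| 3 / 0 | 0.19 | 0.126 |

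The direction can also reverse. With a true benefit of 0.5 SD and one removal threshold for both arms, more controls are removed. If 5%, 10% or 20% of controls go, the expected difference among those remaining is 0.43, 0.39 or 0.33 SD, so the effect is understated by 0.07 to 0.17 SD. The document does not state this removal mechanism, so these figures are an upper-end illustration.

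**The case against.** The strongest reply is that the main analysis set is nowhere named. The groups are defined by allocation, and analysis sets are commonly left to a statistical analysis plan, which is not shown. That stands in part: the set is implied, and a fuller plan may define it well. But the article does more than stay silent. It states that intention-to-treat is additional and conditional, and a later plan would have to override that sentence.

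Several stronger readings are tempting, and the documents do not support them.

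- *Patients are removed because of their primary outcome.* The rule concerns recurrence and clinical worsening. It does not mention varus angle, plantar pressure or contact area. A link with gait is likely but not stated.
- *Discontinued patients are never measured.* Those who worsen after week 4 already have a 4-week value. Later assessment is not forbidden; it is only unmentioned.
- *Non-adherence, crossover or withdrawal by the study would not trigger the intention-to-treat analysis.* Loss to follow-up is not defined, and a discontinued patient could count as lost. Nothing says that patients who cross over or do not adhere are excluded or moved.
- *Unblinded staff can choose who leaves.* The Randomization section does say "The participants and researchers will know the allocation but the outcome assessors and data analysts will not". But the ethics committee shares the decision after adverse events, and discontinuation for recurrence is stated as a rule, not as a choice.

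It is also fair to say that the bias figures are assumed throughout, and that equal discontinuation with no true effect gives none.

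**Conclusion.** The concern holds in a limited form. As written, intention-to-treat is a conditional extra, patients who recur or worsen leave the study, and no text keeps their remaining assessments. The change analysis therefore loses values from patients whose prognosis is probably worse, and retaining earlier data does not restore them.

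Whether this biases the comparison depends on two things that the article does not give: whether discontinuation differs by arm, and how strongly it is related to gait outcome. Under the assumed range the bias is 0 to 0.20 SD, against a standard error of 0.26 SD. A reader might infer that the design favours acupuncture. The documents do not support that, because the direction depends on which arm loses more patients.

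This should be fixed. It is not a fatal flaw, since the size is conditional and the trial is a pilot. Still, the remedy is small, and assessments not made cannot be recovered later.

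**What to change.** 1. In the Statistical analysis section, state that the main analysis compares all randomised patients in their assigned group. Any completer or per-protocol analysis is supplementary.
2. Reconcile the Informed consent, Adverse Events and Statistical analysis sections so that stopping trial treatment is distinct from ending data collection. Keep the 4-week and 3-month assessments already scheduled for patients who stop treatment, where they are able and willing.
3. Report discontinuations and their reasons by arm.

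The clinical decision on when treatment stops is unchanged.

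**Cost.** This takes a few sentences and uses visits already planned. Recruitment is under way (Trial status), and a protocol change needs a written application to the ethics committee (Ethics), so an amendment is required. A few assessments will be harder to obtain, especially from patients sent elsewhere for treatment, and the estimated effect may be slightly diluted.

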## Discussion

Acupuncture is a frequently used therapy for stroke rehabilitation in China, but the evidence of effect from previous studies seemed to be inconclusive [21]. Some systematic reviews have been done to study the effect of acupuncture for stroke rehabilitation [22–25]. These reviews have drawn consistent conclusions that acupuncture appeared to be safe and effective for stroke rehabilitation, but the benefits required further confirmation with larger, more transparent and well-conducted randomized clinical trials.

The complexity of stroke symptoms might be one of the possible reasons for previous studies and reviews concluding inconclusive results. A series of symptoms such as aphasia, apraxia, shoulder pain, cavovarus foot, limb numbness, and body imbalance will appear after the onset of stroke. It is difficult for acupuncture treatment to cover all symptoms of stroke rehabilitation. Thus, it would be reasonable to focus on certain aspects when investigating the effect of acupuncture for stroke rehabilitation. Previous studies and reviews indicated that acupuncture, when combined with conventional rehabilitation therapies, is effective in treating poststroke shoulder pain [26] and aphasia [27, 28], and improving poststroke imbalance [29] and quality of life [30]. In the current study, we will focus on the effect of acupuncture for cavovarus foot, which is one of the main poststroke symptoms risking patients’ daily life. We hope to reveal the real effect of acupuncture by focusing on one certain symptom rather than the whole stage of stroke rehabilitation.

Lack of objective quantitative assessments might be another reason affecting the quality of previous results. In the current study, we intend to study the effect of acupuncture for poststroke cavovarus foot with objective biomechanical outcome measurements from the RSScan gait system. The RSScan gait system was originally designed to provide objective biomechanical parameters for the adjustment of athletes’ movements to maximize their performance [16]. Recently, it has also been used in clinical studies of diabetes [17], multiple sclerosis [18], and knee osteoarthritis [31] to provide quantitative assessments and achieved satisfied results. Our group has tested the feasibility of applying RSScan gait system in the evaluation of stroke rehabilitation [32]. Thus, we believe that objective biomechanical results from the current study will provide more detailed interpretations of the effect of acupuncture for stroke rehabilitation, especially for poststroke cavovarus foot.

We present the protocol of a pilot randomized controlled trial aims at evaluating the biomechanical effect of acupuncture for poststroke cavovarus foot. Results of the current study will provide detailed interpretations of the biomechanical effect of acupuncture for stroke rehabilitation and foundations for future larger clinical studies.

